#### **10.4 Emergency Unblinding**

During the double-blind phase of the trial, in the event of a valid medical or safety reason (e.g. in the case of an SAR where it is necessary for the investigator or treating health care professional to know which treatment the participant is receiving before the participant can be treated), the responsibility to break the treatment code resides with the treating clinician or a delegated member of the trial team. The chief investigator and co-lead investigator may be approached for emergency unblinding.

The online randomisation system will also be used for emergency unblinding. Appropriately trained and delegated site staff will be given the necessary access rights and permissions to access this facility. The name, contact details of the unblinder and reason for unblinding will be recorded within the system. An email stating that an unblinding has taken place will be automatically sent to the coordination team for oversight purposes. Site pharmacists may carry out emergency unblinding if the web based randomisation system is not available.

#### **10.5 Accountability and Dispensing**

##### *10.5.1 Pharmacy responsibilities*

Sites will maintain a full accountability record documenting receipt, storage, dispensing, return and destructions as appropriate, as specified in the pharmacy manual.

There will no accountability records maintained for nIMPs listed in section 10.3.

### **11 PROCEDURES AND ASSESSMENTS**

#### **11.1 Participant Identification**

The trial will recruit adult patients with NS due to primary MCD/FSGS. Patients will be identified by local nephrologists from histology meetings and internal database review within each Renal Unit. Potential participants will be approached by their direct clinical care team in the first instance.

The trial will be publicised on the trial-specific website managed by the central co-ordination team at Cambridge Clinical Trials Unit, and via Patient View. Patient View gives patients secure access to their healthcare records including blood and urine results and diagnoses. Patients can also see trials for which they may be eligible - TURING will be visible to all patients who use this service and have been diagnosed with FSGS/MCD.

## 11.2 Consent

The Informed Consent form (ICF) must be approved by the REC and must be in compliance with GCP, local regulatory requirements and legal requirements. The investigator or designee must ensure that each trial participant is fully informed about the nature and objectives of the trial and possible risks associated with their participation.

The investigator or designee will obtain written informed consent from each participant before any trial-specific activity is performed. The ICF used for this trial and any relevant change made during the course of this trial, must be prospectively approved by the Research Ethics Committee (REC). The investigator at each site will retain the original of each participant signed ICF.

Should a participant require a verbal translation of the trial documentation by a locally approved interpreter/translator, it is the responsibility of the individual investigator to use locally approved translators.

Any new information which becomes available, which might affect the participant's willingness to continue participating in the trial will be communicated to the participant as soon as possible.

### *11.2.1 Recruitment to RaDaR and other research studies including NephroS*

At screening, all participants will be enrolled in RaDaR. RaDaR is a registry study that collects laboratory data from patients with kidney disease. Data from patients enrolled in the RaDaR trial will be uploaded to the TURING trial database at the end of the TURING trial to improve completeness of the dataset. It will allow on-going data collection to be performed remotely after participants have completed the active phase of the trial, particularly with regard to long term effect on kidney function and progression to ESKD.

RaDaR data will be requested by the central team and patient identifiers will be required initially to link the RaDaR database with the TURING database. This identifiable information will be stored in the secure data hosting server hosted by the University of Cambridge and will only be accessed to ensure the correct participant is being linked with the correct record. Local trial teams will initially collect the identifiers on the eCRF but this information will not be visible to them after they have completed the required tabs in the e-CRF.

If available at the participating centre, participants will also be offered enrolment in PatientView. This not only allows patients to view their own results, but also allows the automatic capture and collation of results via RaDaR.

Participants will also be offered the opportunity to take part in other observational trials such as National Study of Nephrotic Syndrome (NephroS, REC number 09/H0106/90). This UK wide registry is an observational study of steroid-resistant and sensitive MCD/FSGS which

aims to provide a comprehensive genotype/phenotype correlation of MCD/FSGS. Recruiting trial participants into NephroS will allow blood and urine samples to be banked for future potential biomarker studies.

### 11.3 Screening Evaluation

#### *11.3.1 Screening and Day 0*

Screening and Day 0 (SPPR) visits may be performed separately, within a period of four weeks, or in a single combined visit wherever possible. Patients will start treatment with the pre-specified prednisolone regime (see Section 10.3) at the Day 0 (SPPR) visit, which may occur simultaneously with the screening visit if the treating clinician considers this clinically appropriate according to usual care. This may be before all data are available to determine eligibility.

Patients who have started Standard of Care treatment with prednisolone prior to consent may be enrolled in the trial if:

- the prednisolone was started within 4 weeks,
- the dosing used is consistent with the SPPR (section 10.3.1),
- patients are randomised and receive IMP within 4 weeks of starting SPPR.

In this situation, Day 0 would be when they started treatment with prednisolone for new onset/relapse of nephrotic syndrome. For these patients, serum albumin and urinary PCR tests will have been performed within the 7 days preceding SPPR (i.e. Day 0 -7). Patients may have been receiving more than 60mg prednisolone daily prior to randomisation. These patients are still eligible for the trial (if they have been receiving this dose for less than 4 weeks). In this group of patients, the prednisolone will be reduced to 60mg within 48 hours of randomisation.

Eligible participants will subsequently be randomised by a suitably trained and delegated member of the research team as described in Section 9.3 and the trial manual.

Trial visits, including screening and Day 0 assessments will be performed at the outpatient clinics.

Trial specific assessments will only be conducted after participants have given written informed consent. Where possible, eligibility blood and urine results will be obtained from standard of care visits.

Participants will be provided a container to collect 24 hour urine sample which they may bring back to the clinic during their next visit (< 4 weeks from Day 0). It is recommended that participants collect all urine produced starting from second urine of any day up until first urine of the following day.

Screening and Day 0 (SPPR) visits (which may be combined or occur over a period of up to 4 weeks) will include the following assessments:

- Demographics information
- Relevant medical history
- Height and weight

- Blood pressure
- Haematology
- Biochemical analysis
- Serum pregnancy test (if appropriate for female participants)
- Immunoglobulins G and M
- Urinary PCR
- Serology for hepatitis B, C and HIV
- Health status questionnaire: EQ-5D-5L
- Additional Health Costs questionnaire: out of pocket expenditure related to kidney disease over the previous 3 months, employment status, work productivity and activity impairment questionnaire, carer time
- A 24 hour urine collection for proteinuria
- Concomitant medications – see section 10.3.3
- Adverse event review
- Prednisolone dosing
- CNI dosing (if applicable)

Subsequent visit timings are based on the date of Day 0 (SPPR) i.e. when the standard prednisolone regime is started for treatment of the new onset/relapse of nephrotic syndrome, except for the post-remission assessments.

#### **11.4 First and second dose of IMP**

Within 4 weeks of Day 0 (SPPR), participants are expected to have the first dose of treatment administered. This may be a research visit at which only the IMP administration will take place, or may be combined with a trial visit if appropriate.

The second dose of IMP should be scheduled for two weeks after the first IMP dose, however a window of -1 week or +2 weeks can be utilised.

If appropriate for female participants, serum or urinary pregnancy tests will be carried out ≤ 14 days before each IMP infusion and recorded in the CRF.

No additional procedures will be mandated at these two visits; however AEs and concomitant medications will be assessed as standard. These visits may also be combined with trial visits if appropriate.

#### **11.5 Pre-remission trial visits – aligned with standard of care**

The following tests will be carried out every 4 (+/- 1 week) weeks until remission is achieved or until Week 16, whichever is earlier:

- Weight
- Blood pressure
- Haematology
- Biochemical analysis
- Urinary PCR
- 24 hour urine collection for proteinuria –week 16 only
- Concomitant medications - see section 10.3.3
- AE assessments

- Health status questionnaire: EQ-5D-5L
- Additional Health Costs questionnaire – week 16 only
- Prednisolone dosing
- CNI dosing (if applicable) at weeks 4, 8, 12, and 16

These procedures may be performed at a single visit, or may take place over a period of up to two weeks.

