### 9.5.2 *Duration of safety reporting*

Safety reporting of SARs/SUSARs is required for trial participants withdrawn from trial treatment (including those withdrawn from trial treatment eg for non-response) for a minimum of 12 months following the last dose of IMP. Rituximab causes B cell depletion, with B cell recovery beginning within 6 months. By 12 months after treatment, B cell counts have generally returned to normal (Truxima SmPC).

If a trial participant has withdrawn his/her consent all trial-specific tests and assessments should be stopped from the point of withdrawal, including safety reporting.

They should be followed up by their treating clinicians until the event resolution but no new data should be collected from them for the trial purposes

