#### 11.5.1 Week 16 Visit

Patients who have not responded to treatment by achieving partial or complete remission at the week 16 visit (16 weeks from Day 0, +/- 1 week) will leave the trial and return to standard of care treatment. These patients will not receive the third dose of rituximab or placebo at week 26 as they have not demonstrated steroid responsiveness, and on-going treatment with prednisolone with or without rituximab is likely to be futile.

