| Immunoglobulins G & M                    |                                          | x                        |                                  |                   |                    |                                 | x                      |                               |                               |                                | x                                 |                                                                                    | x                                                 | x                    |
| Urinary PCR                              | x                                        |                          | x                                | x                 | x                  | x                               | x                      | x                             | x                             | x                              | x                                              |                                                                                    | x                                                 | x                    |
| 24 hour urine collection for proteinuria |                                          | x                        |                                  |                   |                    | x                               | x                      |                               |                               |                                |                                                | x                                                                                  | x                                                 | x                    |
| Serology for hepatitis B,C and HIV       |                                          | x                        |                                  |                   |                    |                                 |                        |                               |                               |                                |                                                |                                                                                    |                                                   |                      |

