7. Serum pregnancy test required for eligibility. The week 24 visit will be performed in the 2 weeks prior to administration of IMP, or the same day, and can be combined with a post remission trial visit if appropriate. Serum or urine pregnancy needs to be carried out ≤ 14 days before IMP administration in all women of child-bearing potential.
8. Participant should be withdrawn from the trial in case he/she hasn't achieved partial remission by week 16.
9. Optional dipstick testing encouraged for patients in complete remission only. See section 11.7 for further details.
10. Additional Health Cost Questionnaires performed 6 monthly in these visits.
11. AE assessments/ Con med check will be carried out in clinic visits before prescription for IMP infusion is given. They will not be checked on day of infusion unless combined with another trial visit. Trial participants withdrawn from treatment will require safety reporting (SAR/SUSAR only) for up to 12 months post last IMP dose.
12. Ig G & M done 6 monthly at these visits

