#### *13.3.3 Adverse events of special interest*

A number of adverse events of special interest have been identified as being possibly related to trial treatment (rituximab) and non-IMP (glucocorticoids or CNIs). – These will be monitored for the duration of the trial. These AESIs are as follows:

Related to trial treatment (Rituximab):

- Systemic infusion/injection reactions
- Hypogammaglobulinaemia (IgG <400 mg/dL (Grade 3) and <250 mg/dL (Grade 4))
- Hypersensitivity reactions

Possibly related to the IMP (Rituximab) or non-IMP (glucocorticoids or CNIs):

- Infections requiring antimicrobial, antiviral or antifungal treatment (including opportunistic, Progressive multi-focal leukoencephalopathy)
- Malignancy

Possibly related to non-IMP (glucocorticoids or CNIs):

- New onset Diabetes Mellitus
- Osteoporosis/fracture
- Peptic ulceration/gastritis requiring medication/endoscopy
- Glaucoma
- Cataracts
- Weight gain > 10% (not attributed to oedema)
- Mood changes requiring medication

Hospital admissions – Only those related:

- D1. Hypovolaemia
- D2. Fluid overload secondary to nephrotic syndrome
- D3. Thromboembolic events (due to underlying disease)

Patients with nephrotic syndrome have frequent hospital admissions related to their underlying disease. Hospital admissions related to hypovolaemia or fluid overload secondary to nephrotic syndrome, or to thromboembolic events, will be **exempt from** expedited SAE reporting. However, these events will be designated as Adverse Events of Special Interest and details will be collected in the CRFs.

Each Principal Investigator must report all AESIs to the CI using the CRF in a timely manner. If the AESI is deemed to be serious, then the reporting procedure for an SAE should be followed as detailed in section 13.4, unless the AESI is related to hypovolaemia or fluid overload secondary to nephrotic syndrome.

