## 16 STATISTICS

### 16.1 Statistical Methods

#### 16.1.1 Analysis populations

The following populations will be defined for efficacy and safety analyses:

- **Intent-to-treat population (ITT)**  
The ITT population is defined as all patients randomised in the trial, regardless of whether they actually received treatment. The treatment group will be analysed as randomised.
- **Responding patient population**  
Responding patient population is defined as all patients randomised in the trial, received allocated protocol treatment and achieved partial/complete remission. The treatment group will be analysed as randomised.
- **Safety population**  
The safety population comprises all patients randomised and having received at least one dose of trial treatment. The treatment group will be analysed as treated.

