#### *16.1.4 Safety analysis*

The safety analyses will be based on the safety population. All safety parameters will be summarised. Summary tables will be presented for incidence rates (number of patients with at least one incidence) of, AESIs, and SAEs.

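### Participants not in remission at week 16, about a quarter of those randomised, have no scheduled IgG after dosing but still count in the incidence of an adverse event defined by IgG

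*Protocol*

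**What the plan says.** - **Pre-remission visits.** Section 11.5 sets tests every 4 weeks "until remission is achieved or until Week 16, whichever is earlier". Immunoglobulins are not on its list.
- **Schedule table.** In table 11.15 the row "Immunoglobulins G & M" is marked at eligibility, remission, the 3-monthly post-remission visits (6-monthly by footnote 12), month 24 and relapse. It is blank at weeks 4, 8, 12 and 16.
- **No other panel covers IgG.** Footnotes 5 and 6 limit haematology to neutrophils and lymphocytes, and biochemistry to urea, creatinine, eGFR and albumin. Section 11.4 mandates no further procedures at the first two infusions.
- **Exit at week 16.** Under section 11.5.1, participants without partial or complete remission "will leave the trial and return to standard of care treatment". Section 11.12 makes week 16 their final visit.
- **After exit.** Section 9.5.2 continues SAR and SUSAR reporting for treatment withdrawals, "including those withdrawn from trial treatment eg for non-response". Footnote 11 of table 11.15 says: "Trial participants withdrawn from treatment will require safety reporting (SAR/SUSAR only) for up to 12 months post last IMP dose".
- **The event.** Section 13.3.3 lists hypogammaglobulinaemia among the AESIs related to rituximab and defines it by IgG below 400 mg/dL (grade 3) or 250 mg/dL (grade 4).
- **The analysis.** Section 16.1.1: "The safety population comprises all patients randomised and having received at least one dose of trial treatment". Section 16.1.4: "Summary tables will be presented for incidence rates (number of patients with at least one incidence) of, AESIs, and SAEs".

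**The concern.** An event defined by a laboratory value can be counted only where the value is measured. Here every scheduled post-baseline measurement depends on first reaching remission. Dosed non-remitters therefore enter the denominator for this AESI with no scheduled route into the numerator.

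Two consequences follow. The incidence of a recognised rituximab risk may be understated. The between-arm comparison also depends on remission, which occurs after randomisation and is itself a secondary outcome (section 8.6.2): if the arms remit at different rates, different shares of each arm are tested.

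This is a matter for the protocol, because the sampling schedule is fixed there and an analysis plan cannot supply samples that were never taken.

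**Working it through.** **1. The protocol's planning figure.** Section 16.2 assumes 75% remission and 5% non-compliance: 112 × (0.75 − 0.05) = 112 × 0.70 = 78.4, matching the 78 remitters required. The implied non-remission share is 1 − 0.75 = 0.25.

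**2. Participants affected.** Inputs are 130 to 150 enrolled, 5% early dropout before remission assessment (both section 16.2) and 1:1 allocation (section 8.1).

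| Enrolled | Dropout removed | Calculation | Non-remitters | Per arm (÷ 2) |
|---|---|---|---|---|
| 130 | yes | 0.25 × 130 × 0.95 | 30.9 | 15.4 |
| 130 | no | 0.25 × 130 | 32.5 | 16.3 |
| 150 | yes | 0.25 × 150 × 0.95 | 35.6 | 17.8 |
| 150 | no | 0.25 × 150 | 37.5 | 18.8 |

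That is about 31 to 38 in total and 15 to 19 on rituximab. Those never dosed fall outside the safety population. If the 5% non-compliance also meant no dose, the lower figure becomes 0.25 × 130 × 0.95 × 0.95 = 29.3. The split by arm applies one pooled rate to both arms. If true remission were 65% to 85% (an assumption), the total would run from 0.15 × 130 = 19.5 to 0.35 × 150 = 52.5.

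**3. Possible understatement (illustration only).** Let *p* be the true rate in remitters and *kp* the rate in non-remitters. Suppose scheduled tests find every case in remitters and no case is found in non-remitters. The observed rate is 0.75*p*, the true rate is 0.75*p* + 0.25*kp*, and the relative understatement is 1 − 0.75 / (0.75 + 0.25*k*).

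| *k* (assumed) | Understatement |
|---|---|
| 0.5 | 14% |
| 1 | 25% (a true 10% reads 7.5%) |
| 2 | 40% |
| 3 | 50% |

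The protocol gives no value for *k*, so none of these is an estimate.

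**4. Whether week 16 is a sensible time to test.** Dose 1 falls at weeks 0 to 4 and dose 2 two weeks later, at weeks 2 to 6 (section 10.1.7). The week 16 visit is then 16 − 6 = 10 to 16 − 2 = 14 weeks after dose 2. With the permitted windows, dose 2 falls at weeks 1 to 8 and the visit at weeks 15 to 17, giving 15 − 8 = 7 to 17 − 1 = 16 weeks. This lies inside the 6 months within which section 9.5.2 says B cell recovery begins.

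**5. Other sources of IgG.** A low value from a clinically prompted test before exit would be recorded, since section 13.3.2 keeps laboratory results that meet an AESI definition. RaDaR supplies laboratory data (section 11.2.1), but the analytes named as coming through it (table 11.16, footnotes 2 and 3) are neutrophils, lymphocytes, urea, creatinine, eGFR and albumin. IgG is not among them.

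**The case against.** The strongest reply is that the loss comes from a deliberate exit rule. Non-remitters stop contributing all non-serious AESIs after week 16, and the protocol justifies the exit because further treatment is likely to be futile. One IgG at week 16 would not make them comparable with remitters, who are tested repeatedly and can receive a third dose. Clinically important cases keep a route: adverse events are assessed at each pre-remission visit, treated infections are a separate AESI, and serious reactions stay reportable after withdrawal. The size of the bias is unknown, no dosing rule uses IgG, and showing the number tested is a matter for the analysis plan.

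Much of this is fair. The remedy is partial, the effect cannot be sized, and a tested denominator could be specified in the analysis plan. The exit rule does not explain the gap before week 16, however. Over those weeks the other AESIs are assessed at every visit in everyone, while this one is not measured until remission. A tested denominator would disclose that gap without filling it.

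Section 9.5.1 does say that consenting patients should remain in follow-up, but that sentence sits with the item on missed infusion visits. The synopsis, section 11.5.1, section 11.12 and footnote 8 of table 11.15 all end participation for non-remitters.

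**Conclusion.** The concern holds. Dosed participants not in remission at week 16 have a screening IgG and no scheduled IgG afterwards, yet they count in the denominator for an IgG-defined AESI. On the 75% planning rate this is about 31 to 38 participants, of whom 15 to 19 were allocated rituximab, assuming equal remission in both arms and that nearly all were dosed. The direction is towards understatement; its amount, and any between-arm bias, cannot be derived from the protocol. Cases in this group can still surface through unscheduled testing. The primary outcome, sample size and dosing decisions are untouched. The change should be made because it is cheap and the data cannot be recovered later.

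A separate, editorial point is that the synopsis places IgG and IgM at week 26 and then 6-monthly. Sections 11.6 and 11.7 and table 11.15 place them at remission and then 6-monthly, and neither section 11.8 nor the Week 24 column lists them. The synopsis relapse row also omits the IgG and IgM that section 11.11 and the table require.

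**What to change.** - Add IgG and IgM to the week 16 visit in section 11.5 and table 11.15. Non-remitters then have one value before and one after dosing. A non-serious fall after week 16 would still be missed.
- Report the hypogammaglobulinaemia AESI by arm with the number who had at least one post-dose IgG. This can sit in the analysis plan.
- Align the synopsis with sections 11.7, 11.8 and 11.11 and table 11.15 on the timing of IgG and IgM, including the relapse row.

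The cost is one extra assay on blood already drawn at week 16, with no added visit, plus a protocol amendment through the approvals in section 19.4. Week 16 visits completed before the amendment cannot be recovered. The synopsis correction is wording only if the synopsis is brought into line with the body text.
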